### Statistical analysis

Intention-to-treat (ITT) will be used for the complete follow-up analysis. All randomized participants who received at least one treatment session and for whom at least one post-baseline assessment will be included for the full analysis in the full analytic dataset (FAS). Missing data will be replaced according to the principle of multiple imputations. Participants demonstrating strict protocol adherence and completing the full treatment course will be included in the Per Protocol Set (PPS) for efficacy analysis. All randomized participants who received at least one treatment will be included in the Safety Analysis Set (SS).

Data management will be performed using Epidata software (v3.1, Odense, Denmark), with subsequent analyses conducted in IBM SPSS Statistics 25.0 (IBM Corp, Version 25.0, New York, USA). Baseline characteristics will be analyzed using FAS, while efficacy outcomes will be evaluated through both FAS and PPS. Safety assessments for acupuncture (Jin’s three-needle) intervention will be utilized SS. Continuous data will be statistically described using mean ± standard deviation and qualitative data will be provided as percentages or proportions, along with confidence intervals of 95%. Outcomes with multiple time points will be analyzed using repeated-measures analysis of variance (ANOVA), with treatment group and follow-up time as fixed effects and individual as a random effect, to compare the effect sizes at each time point. We plan to use the Shapiro – Wilk test to assess the normality of the residuals in the repeated measures ANOVA model. If the normality assumption is violated, we will consider appropriate non – parametric alternatives, such as the generalized estimating equations (GEE) approach. For between-group comparisons, normally distributed data with homogeneous variances will be analyzed using the two independent samples t-test. Non-normally distributed continuous variables or those with heterogeneous variances will be analyzed using the Kruskal-Wallis H test. All Statistical tests will be based on two-sided tests, with a significance level of α = 0.05 for statistically significant results. The Bonferroni test will be used for post hoc pairwise comparisons. We plan to conduct a sensitivity analysis to assess the impact of varying the assumed value of the Minimal Clinically Important Difference (MCID) (within a reasonable range based on existing literature and expert opinion) on the study findings and conclusions.

We will investigate whether acupuncture (Jin’s Three-Needle) regulates aberrant gene expression and DNA methylation patterns in the peripheral blood leukocytes of patients with mild-to-moderate depression. Details on molecular analysis are provided in S4 of the Supplementary File in S1 File.

The final statistical analyses will be conducted by an independent data analyst who is blinded to the treatment group allocation.

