**Methods:**

This is a prospective, parallel-arm, single-blind, randomized controlled trial. We plan to enroll 106 participants with mild-to-moderate depression, randomly assigning them to receive either JTN or sham acupuncture (SA) in a 1:1 ratio. All participants will receive the JTN treatment or SA treatment for 8 weeks (3 per week). The primary outcome will be assessed using the 17-item Hamilton Depression Rating Scale (HAMD-17). Secondary outcomes will include the Self-Rating Depression Scale (SDS), Pittsburgh Sleep Quality Index (PSQI), Hamilton Anxiety Scale (HAMA), Self-Rating Anxiety Scale (SAS), and the Traditional Chinese Medicine Syndrome Score Scale (TCMSS). Evaluations will be performed at baseline and at weeks 4, 6, and 8 after treatment initiation. Statistical analyses will be conducted on both the intention-to-treat (ITT) and per-protocol (PP) datasets.

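### The analysis called intention-to-treat leaves out randomised participants with no session or no assessment from week 4 on, and no all-randomised efficacy set is defined

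*Protocol article*

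**What the plan says.** All of this is in the protocol article.

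- **Label.** Statistical analysis: "Intention-to-treat (ITT) will be used for the complete follow-up analysis". The abstract uses the same term: "Statistical analyses will be conducted on both the intention-to-treat (ITT) and per-protocol (PP) datasets".
- **Set defined.** Statistical analysis describes the FAS as follows: "All randomized participants who received at least one treatment session and for whom at least one post-baseline assessment will be included for the full analysis".
- **Sets used.** Statistical analysis: "Baseline characteristics will be analyzed using FAS, while efficacy outcomes will be evaluated through both FAS and PPS". The abstract's pair (ITT and PP) thus becomes FAS and PPS in the body, so the FAS is the set that carries the ITT label.
- **Missing data.** Statistical analysis: "Missing data will be replaced according to the principle of multiple imputations". The text does not extend this to people outside the FAS.
- **Schedule.** Abstract, Methods: "Evaluations will be performed at baseline and at weeks 4, 6, and 8 after treatment initiation".
- **Baseline.** Under Randomization and allocation concealment, baseline assessments are completed before the envelope is handed over, so every randomised participant should have a baseline HAMD-17.
- **Withdrawal.** Under Safety, two kinds of participant leave the study: those with a severe adverse event attributed to the intervention, and those who start an antidepressant after marked worsening. The latter are followed for safety analyses.

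**The concern.** Intention-to-treat keeps the groups that randomisation formed. The FAS adds two conditions that are settled only afterwards: having had a session, and having been assessed at week 4 or later. At three sessions a week, week 4 is 12 of 24 sessions into treatment, so there is a long interval in which a participant can be lost without any post-baseline score.

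The loss need not be unrelated to arm or outcome. Under the Safety section, a participant who worsens and starts an antidepressant before week 4, or has a related severe adverse event before then, is withdrawn and may have no later efficacy assessment. Such a participant drops out of the set labelled ITT. The arms also differ in needling depth and manipulation, and the acupuncturists are not blinded.

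The plan treats similar people differently. A participant seen at week 4 but not at week 8 has the primary endpoint imputed; one lost shortly before week 4 is removed altogether. Baseline data exist for both and imputation is already planned, so nothing in the design requires the second to be excluded. The planned difference is only 0.97 points, so even a modest bias would count.

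**Working it through.** **Inputs** (Sample size calculation, protocol article): mean HAMD-17 improvement 10.79 (SD 1.40) with JTN and 9.82 (SD 1.80) with sham; type 1 error 0.05 (two-sided, from Statistical analysis); power 0.80; dropout 15%; 53 per group, 106 in total.

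**Step 1: reproduce the plan's figure.** Difference = 10.79 − 9.82 = 0.97. Pooled SD = √((1.40² + 1.80²)/2) = 1.612. The normal approximation gives 43.4, rounded up to 44 per group. The noncentral t gives 45 (power 0.806 at 45, 0.797 at 44). 45/0.85 = 52.9, so 53 per group and 106 in total. The stated figures reproduce, and this point does not affect them.

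**Step 2: formula for the bias.** Let e_A and e_S be the shares of randomised participants excluded from the FAS in the JTN and sham arms. Let D be how many points less the excluded improve than those kept, taken as equal in both arms. An arm whose kept mean is m has an all-randomised mean of (1 − e)m + e(m − D) = m − eD, so the FAS overstates it by eD. For the contrast:

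bias = (e_A − e_S) × D

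If e_A = e_S, the bias is zero.

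**Step 3: how many could be excluded.** Planned dropout is 0.15 × 106 = 15.9. The article does not say how much of it comes before week 4. If 25%, 50% or 100% does (assumption), about 4, 8 or 16 of 106 would be excluded.

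**Step 4: size, with half of dropout early.** Overall share excluded = 0.5 × 0.15 = 7.5%, about 8 participants. The split and D are assumptions.

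| Split of early losses | e_A − e_S | D = 1 | D = 2 | D = 4 |
|---|---|---|---|---|
| Equal | 0 | 0 | 0 | 0 |
| 2:1 | 10% − 5% = 5% | 0.05 (5%) | 0.10 (10%) | 0.20 (21%) |
| All in one arm | 15% − 0 = 15% | 0.15 (15%) | 0.30 (31%) | 0.60 (62%) |

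Entries are HAMD-17 points, with the percentage of 0.97 in brackets. The bias favours whichever arm loses more poor responders.

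**Step 5: consequence for the test.** At 45 per group the standard error is 1.612 × √(2/45) = 0.34. If there were no true difference, a spurious 0.2 points would raise the two-sided 5% error to about 9%, and 0.3 points to about 14%.

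**Step 6: a one-arm extreme against the same loss in both arms.** Four of 53 excluded with no improvement at all shifts the JTN mean by 4/53 × 10.79 = 0.81. The same loss in the sham arm shifts its mean by 4/53 × 9.82 = 0.74. The contrast moves by 0.81 − 0.74 = 0.07 points, or 7.5% of 0.97.

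**The case against.** A full analysis set of this kind is common, and early loss may well be balanced: both arms have the same session schedule, participants are treated in separate rooms with supervised conversation, and sham participants are promised true sessions later. With balanced loss and equal shortfall there is no bias. Participants with no post-baseline score can be imputed only from arm and baseline, so adding them may change the estimate little. All of that stands, and it limits the size of the point. It does not reconcile the ITT label with the set defined. An unseen analysis plan could not keep this FAS as the ITT set and still analyse everyone randomised.

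A reader might infer several stronger things that the article does not support:

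- **That the bias could be about 84% of the planned effect** (0.81/0.97). This moves one arm only, and assumes no improvement in anyone excluded, which is 10.79/1.40 = 7.7 planning SDs below the mean. The same loss in both arms gives 7.5% (Step 6).
- **That imputing everyone removes the bias.** If loss depends on unobserved outcome and baseline does not explain it, imputed values centre near the mean of those kept and the bias remains.
- **That everyone who stops in the first half of treatment is excluded.** Someone who has had a session, stops, and still attends week 4 stays in the FAS.
- **That a baseline table on the FAS hides imbalance.** It shows the arms as analysed; what it lacks is those excluded.
- **That FAS and PPS have equal standing.** The article says "efficacy outcomes will be evaluated through both FAS and PPS" but does not rank them, and ranking is commonly left to the analysis plan.

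**Conclusion.** The point holds as a mismatch between label and definition with a possible, unquantified bias. The set called intention-to-treat excludes randomised participants on two post-randomisation conditions, and no efficacy set includes everyone randomised. The article's own withdrawal rules give a route by which exclusion could relate to outcome or arm.

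The ranges in Step 4 rest on three assumptions that the article does not supply: the share of dropout before week 4, its split between arms, and how much less the excluded improve. They show what could happen and are not a forecast. Severity is should-fix: the correction is simple and worth making, but the documents do not show that the primary result will be materially biased.

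**What to change.** 1. Define the primary efficacy set as all 106 randomised participants, analysed as allocated, whether or not they had a session or a later assessment.
2. Apply the planned multiple imputation to missing week-8 HAMD-17 in that set, with arm and baseline HAMD-17 in the imputation model, together with the week-4 and week-6 scores where they exist.
3. Add a missing-not-at-random sensitivity analysis, for example delta-adjusted imputation with the delta varied separately by arm, because imputation from baseline alone cannot deal with loss that depends on unobserved outcome.
4. Rename the present FAS modified ITT, and keep it and the PPS as supportive analyses.
5. Report baseline characteristics for all randomised participants.

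The cost is a wording change, slightly more analysis work and slightly more imputation uncertainty. No new data are needed and the sample size stays at 106. Trial design gives an anticipated end of 12 December 2026; the change should be made before unblinding, since later it would be post hoc.

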### Outcomes

#### Primary outcome.

The primary outcome is the change in the 17-item Hamilton Depression Rating Scale (HAMD-17) score from baseline to the end of the 8-week treatment period (Week 8). The HAMD-17 is the most employed classical clinical depression symptom rating scale, which measures five domains related to depression, including anxiety/somatization, weight, cognitive disturbance, psychomotor retardation and sleep disturbance [27]. HAMD-17 consists of 17 items that include 3 (scored from 0 to 2) and 5 (scored from 0 to 4) response variants, which reflect ascending symptom severity levels. Total scores are categorized as follows: 0–7 (normal), 8–24 (mild to moderate depressive disorder), and ≥25 (major depressive disorder).

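### The repeated-measures model lists no group-by-time term, so as written it gives one visit-averaged effect rather than the week-8 HAMD-17 contrast, and the plan names no deciding test

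*Protocol article*

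**What the plan says.** The Primary outcome section defines a single time point: "The primary outcome is the change in the 17-item Hamilton Depression Rating Scale (HAMD-17) score from baseline to the end of the 8-week treatment period", that is, week 8. The Sample size calculation section uses the same quantity: a change of 10.79 (SD 1.40) with acupuncture against 9.82 (SD 1.80) with sham, type 1 error 0.05 and type 2 error 0.2, giving 45 per group and 106 in total after 15% dropout.

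The abstract gives the visit schedule: "Evaluations will be performed at baseline and at weeks 4, 6, and 8 after treatment initiation". HAMD-17 is therefore a repeatedly measured outcome.

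For such outcomes the Statistical analysis section prescribes "repeated-measures analysis of variance (ANOVA), with treatment group and follow-up time as fixed effects and individual as a random effect", and the sentence continues with its purpose: "to compare the effect sizes at each time point". No interaction of group with time is named.

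The same section adds, for between-group comparisons, that "normally distributed data with homogeneous variances will be analyzed using the two independent samples t-test", with Kruskal-Wallis where normality or equal variance fails. It names no endpoint or visit for these tests. It also says: "The Bonferroni test will be used for post hoc pairwise comparisons". Nothing states which procedure decides the primary outcome.

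**The concern.** With group and time as the only fixed effects, the model forces the between-arm difference to be identical at every visit. It has one group coefficient, so there are no visit-specific effects to compare, although producing them is the stated reason for fitting it. In balanced data that coefficient is the mean of the differences at the visits included. The primary outcome is the difference at one of those visits.

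If this model were used for the primary result, it would answer a different question from the declared one, with a power that the sample size calculation does not describe. The t-test and Kruskal-Wallis sentences leave other routes open. The model's group term, a model contrast, a t-test and a rank test could each be presented as the main result, and nothing fixes the choice before the data are seen.

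**Working it through.** **Inputs from the protocol article.** Changes of 10.79 (SD 1.40) and 9.82 (SD 1.80), two-sided alpha 0.05, power 0.80, 15% dropout, post-baseline visits at weeks 4, 6 and 8.

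**Step 1: the plan's own figure.** Difference = 10.79 − 9.82 = 0.97. Pooled SD = √[(1.40² + 1.80²)/2] = √2.60 = 1.612. Standardised difference = 0.97/1.612 = 0.60. Power of a two-sample t-test from the noncentral t distribution is 0.797 at 44 per group and 0.806 at 45, so 45 per group is reproduced. Dropout: 45/0.85 = 52.9, rounded up to 53 per group and 106 in total. The sample size is therefore that of a two-sample comparison of the week-8 change.

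**Step 2: what the listed terms estimate.** In a balanced model with group and time only, the group coefficient is (d4 + d6 + d8)/3, where d is the between-arm difference at each visit. A least-squares check on simulated data (20,000 participants, effect growing linearly to 0.97 at week 8) gave 0.73 for the group coefficient without the interaction and 0.97 for the week-8 contrast with it.

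**Step 3: size of the mismatch.** The article gives no week-4 or week-6 effects and no correlation between visits. Both are assumed here, as is an SD of 1.612 for the change at every visit.

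- Averaged effect, flat: 0.97 (100% of the week-8 effect)
- Linear growth: 0.97 × (0.50 + 0.75 + 1)/3 = 0.73 (75%)
- Late onset: 0.97 × (0.25 + 0.50 + 1)/3 = 0.57 (58%)
- Week 8 only: 0.97 × (0 + 0 + 1)/3 = 0.32 (33%)

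The SD of a participant's three-visit mean with common correlation ρ is 1.612 × √[(1 + 2ρ)/3]: 1.56 at ρ = 0.9 and 1.18 at ρ = 0.3. The noncentrality is the averaged effect divided by (that SD × √(2/45)), on 88 degrees of freedom. For linear growth at ρ = 0.9 this is 0.7275/(1.558 × 0.2108) = 2.22, which gives power 0.591.

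| Assumed trajectory | ρ = 0.9 | ρ = 0.7 | ρ = 0.5 | ρ = 0.3 |
|---|---|---|---|---|
| Flat | 0.832 | 0.884 | 0.933 | 0.972 |
| Linear growth | 0.591 | 0.658 | 0.736 | 0.826 |
| Late onset | 0.399 | 0.453 | 0.523 | 0.616 |
| Week 8 only | 0.164 | 0.183 | 0.211 | 0.251 |

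The comparator is 0.806 for the week-8 difference at 45 per arm. Averaging lowers the variance, so it gains power when the effect is flat. It loses power when the effect builds up late. Only in the flat case does it estimate the declared quantity.

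**The case against.** The best defence is that the list of terms is merely incomplete. The purpose clause points to visit-specific contrasts, an interaction is a standard part of a two-group repeated-measures ANOVA, and a journal article condenses. This may well be what was meant. It does not remove the point: the article states the fixed effects explicitly, and those terms cannot do what the same sentence asks of them. Covariance structure is different. It is ordinary analysis-plan detail and no error here.

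A reader might go further and infer that the trial cannot test its primary endpoint, or that its 80% power is lost. The documents do not support that. The two-sample t-test in the same section can be applied directly to the week-8 change, and it reproduces the 45 per group. What is missing is a statement that this test, or any other, is the deciding one.

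A reader might also infer that Bonferroni over three visits cuts week-8 power to 66% (alpha 0.05/3 = 0.0167, 45 per arm). The arithmetic is right but the premise is not established. The correction is confined to post hoc comparisons, which need not include the primary test, and it could refer to contrasts between visits within an arm. It would also require visit-specific between-arm tests, which a model without the interaction does not supply, so this loss cannot be added to the loss from averaging.

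Finally, the direction of the power change is not fixed by the documents. With a flat effect, averaging gains power. Even with linear growth, power reaches 83% at a correlation of 0.3.

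**Conclusion.** The point holds for the model as specified: its listed terms contradict its stated purpose and do not isolate the week-8 HAMD-17 change. It also holds that the article leaves open whether a model term, a model contrast, a t-test or a rank test decides the primary outcome.

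The mismatch in what is estimated is present for every non-flat trajectory. Its consequence for power cannot be settled from the article. It ranges from a gain (83%-97%, flat) to a clear loss (40%-62%, late onset), with 59%-83% for linear growth, against 80.6%. These ranges rest on assumed trajectories, correlations of 0.9 down to 0.3, equal SDs at all visits and 45 complete participants per arm. The sample size itself is reproduced and is not affected.

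**What to change.** Keep the repeated-measures rule for all the scales, so that the secondary outcomes retain their analysis, and add the group-by-visit interaction to its fixed effects. Then state four things:

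- The single primary test is the between-group contrast at week 8 in HAMD-17 change from baseline, taken from this model, at two-sided alpha 0.05.
- The t-test/Kruskal-Wallis rule does not compete with that contrast for the primary outcome.
- Bonferroni applies to post hoc comparisons only and not to that contrast.
- The week-4 and week-6 contrasts are secondary.

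An unstructured within-participant covariance is an option rather than a required correction. Only analysis wording changes: data collection, participants and sample size stay as they are. The article describes the trial as still recruiting, with an anticipated end on 12 December 2026, so the change can be made and dated before unblinding.

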### Inclusion criteria

Participants who meet the following criteria will be included.

① Patients who fit the diagnostic criteria for depression in the Diagnostic and Statistical Manual of Mental Disorders(DSM-5);② Patients with a HAMD-17score between 8 and 25.③ Patients between the ages of 18 and 65 years;④ Patients are voluntary and able to sign informed consent.

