### Randomization and allocation concealment

Researchers who are unaware of the trial will use SAS statistical software (SAS Inc., NCSU, version: 9.4, USA) to generate random numbers. The randomization sequence will be created using permuted blocks with a 1:1 allocation ratio (block size = 4) through a computer-generated process. The block size shall not be revealed until the end of the trial. Participants will be informed that they have an equal chance to be assigned to the acupuncture (Jin’s Three-Needle) group or sham acupuncture group.

All the randomization number will be placed in opaque, sealed envelopes. After eligible participants sign the informed consent form and complete baseline assessments, they will receive a sealed envelope with the assigned number. Allocation concealment will be strictly implemented through an independent procedure conducted by an independent researcher at the clinical site, maintaining strict separation between randomization and outcome evaluation processes.

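### No efficacy analysis named in the article conditions on baseline HAMD-17; the comparison is valid and adequately powered as planned, but it gives up precision that costs nothing to recover.

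*Protocol article*

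**What the plan says.** The Primary outcome section states: "The primary outcome is the change in the 17-item Hamilton Depression Rating Scale (HAMD-17) score from baseline to the end of the 8-week treatment period". The Statistical analysis section names four methods for efficacy:

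- For outcomes with several time points, a "repeated-measures analysis of variance (ANOVA), with treatment group and follow-up time as fixed effects and individual as a random effect".
- Generalised estimating equations, if the residuals of that model are not normal.
- For between-group comparisons, "normally distributed data with homogeneous variances will be analyzed using the two independent samples t-test".
- The Kruskal-Wallis test, where normality or equal variance fails.

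None of these is given a baseline covariate, and no ANCOVA or adjusted analysis is mentioned. The Sample size calculation section likewise compares unadjusted mean changes.

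The covariate will be available. The Abstract says: "Evaluations will be performed at baseline and at weeks 4, 6, and 8 after treatment initiation". The Randomization section puts the baseline assessment before allocation: "After eligible participants sign the informed consent form and complete baseline assessments, they will receive a sealed envelope with the assigned number". The inclusion criterion is "Patients with a HAMD-17score between 8 and 25". The sequence uses permuted blocks of four, and no stratification by severity is described.

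**The concern.** Baseline severity is usually among the better predictors of a later score on the same scale. Here it is recorded on every participant, and the entry range is wide. The described allocation does not balance it, and the described analysis does not use it.

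A change score does not replace adjustment. Subtracting baseline forces its coefficient to be exactly 1, whereas ANCOVA estimates that coefficient. Unless the true coefficient is 1, the change-score contrast has a larger variance than it needs, and part of any chance difference between the arms at baseline stays in the estimate.

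The planned difference is under one HAMD-17 point, and the trial is sized at the customary 80% power with little reserve. Precision that can be had without further recruitment is worth taking.

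**Working it through.** **Inputs from the article.** Mean change is 10.79 (SD 1.40) with acupuncture and 9.82 (SD 1.80) with sham. Alpha is 0.05 two-sided and the type 2 error is 0.2. The plan has 45 evaluable per arm, 15% dropout and 53 randomised per arm.

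**Inputs not in the article.** These are rho, the baseline SD, and whether the variances at baseline and week 8 are equal. I assume equal variances and vary the other two. As a guide to the upper end, a uniform spread over 8 to 25 would have SD 17/√12 = 4.9.

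**Step 1: reproduce the plan.** The difference is 10.79 − 9.82 = 0.97. The pooled SD is √((1.40² + 1.80²)/2) = 1.612. The standardised effect is 0.97/1.612 = 0.602. Noncentral-t power is 79.7% at 44 per arm and 80.6% at 45, so 45 is the minimum, as stated. Dropout gives 45/0.85 = 52.9, so 53 per arm and 106 in total. The plan's figures hold for an unadjusted t-test on change.

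**Step 2: variance after adjustment.** With equal variances, Var(ANCOVA)/Var(change) = (1 − rho²)/(2 − 2rho) = (1 + rho)/2.

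**Step 3: the baseline SD that goes with each rho.** Var(change) = 2 × SD² × (1 − rho). Holding the change SD at 1.612 therefore ties the two unknowns together: SD = 1.612/√(2(1 − rho)), or rho = 1 − 1.612²/(2 × SD²).

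| rho | implied baseline SD | variance ratio | power at 45 per arm |
|---|---|---|---|
| unadjusted | – | 1 | 80.6% |
| 0.3 | 1.4 | 0.65 | 93.8% |
| 0.5 | 1.6 | 0.75 | 90.3% |
| 0.7 | 2.1 | 0.85 | 86.5% |
| 0.856 | 3 | 0.928 | 83.4% |
| 0.948 | 5 | 0.974 | 81.6% |

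The large gains belong to a narrow baseline spread. A spread of 3 to 5 points, which fits the entry range more easily, gives a variance saving of about 7% to 3%.

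**Step 4: chance imbalance.** At 53 per arm, one standard error of the baseline difference is SD × √(2/53): 0.58 points at SD 3 and 0.97 at SD 5. The change-score contrast carries (1 − rho) of it:

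- SD 3: 0.144 × 0.58 = 0.08 points, or 9% of 0.97.
- SD 5: 0.052 × 0.97 = 0.05 points, or 5% of 0.97.

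The article does not say whether the t-test is run on change or on raw week-8 scores. On raw scores the share carried is rho: 0.856 × 0.58 = 0.50 points at SD 3, and 0.948 × 0.97 = 0.92 at SD 5.

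**The case against.** **The primary outcome already subtracts baseline.** This is largely right as to size. Under the planned SDs and a baseline SD of 3 to 5, subtraction removes most of an imbalance, and little is left for ANCOVA to gain. It is still not conditioning on baseline, and the article does not tie the t-test to the change score.

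**Covariates are commonly left to the SAP, and this is a condensed article.** That would answer the point if the article were silent on the model. It is not: it lists the fixed and random effects and names the tests, and baseline is not among them. Whether baseline enters the repeated-measures ANOVA as one of the time levels is not stated, but that would not make it a covariate either.

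**Stronger readings that a reader might infer.** The document does not support these three:

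- *That the result would be biased or the test invalid.* Under randomisation the unadjusted estimate is unbiased, and its standard error already allows for chance imbalance.
- *That change must depend strongly on baseline, because someone entering at 8 cannot improve by more than 8, which is below both planned means.* A cap limits the largest possible change; it does not give a slope. The planned SDs of 1.40 and 1.80 leave little room for strong dependence on a widely spread baseline. If the cap matters, it calls the planning assumptions into question, which is another matter.
- *That a typical imbalance could move the result by a third to a half of the planned effect.* For change scores this would need a slope of about 0.5 together with a baseline SD of 3 to 5. With slope 0.5, baseline alone contributes 0.5 × SD to the SD of change, which exceeds 1.612 for any baseline SD above 1.612/0.5 = 3.22. Most of that range contradicts the plan's own figures.

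**Conclusion.** The point stands as a loss of precision, not as an error of validity. The sample size reproduces and the planned 80% power is met without adjustment. What the plan forgoes runs from about 1 to 3 percentage points of power (baseline SD 5 to 3) up to about 13 points (rho 0.3, baseline SD 1.4). The matching one-standard-error shift in the change-score contrast at SD 3 to 5 is 0.05 to 0.08 points. It would be several times larger if raw week-8 scores were compared.

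These figures rest on equal variances at baseline and week 8 and on the planned change SD. Neither rho nor the baseline SD can be recovered from the article, so no single figure for the gain is justified. That the listed analyses omit baseline is certain; how much this costs is not.

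**What to change.** Name one primary analysis for HAMD-17 that includes baseline HAMD-17 as a continuous covariate. This can be an ANCOVA at week 8 or a mixed model over weeks 4, 6 and 8. In the mixed model, add a baseline-by-visit term so that the effect of baseline may differ between visits. Report the adjusted week-8 difference with its 95% confidence interval. Whether the dependent variable is the week-8 score or the change makes no difference to the adjusted treatment effect, so the primary outcome can keep its definition. Treat SDS, PSQI, HAMA, SAS and TCMSS in the same way, each with its own baseline.

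The cost is a sentence or two in the Statistical analysis section and about one degree of freedom in the ANCOVA. No new data are needed, and the planned 106 participants can stay. Recruitment is under way, so the change should be dated and recorded before the analyst sees outcome data by group.
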